**- Determination of the affected coronary pattern.**

Once the parameters have been obtained, the angina pattern corresponding to each patient will be determined, based on the values of FFR, CFR and IMR, and the treatment corresponding to the findings obtained will be carried out. The decision of medical, percutaneous, or surgical treatment of epicardial coronary lesions leading to ischemia will be made on the basis of FFR.

Macrovascular involvement will be defined when the FFR value is ≤ 0.80 and microvascular involvement when the IMR value is ≥ 25 or the CFR is < 2.0 in the presence of an FFR > 0.80. Angina patterns will depend on the different combinations according to coronary compartment involvement, namely Group 1 (Macrovascular and Microvascular Angina); Group 2 (Macrovascular Angina); Group 3 (Microvascular Angina); and Group 4 (Noncoronary Chest Pain). Since the present protocol also considers an approach to the study of coronary spasm, an additional group will be considered, through the evaluation of the acetylcholine test in patients presenting microvascular angina or noncoronary chest pain (Groups 3 and 4). Patients presenting macro or microvascular spasm in this test will be included in Group 5 (Macro or Microvascular Spastic Angina).

**SCIENTIFIC INTEREST OF THE RESEARCH.**

The present research proposal could provide relevant results on the epigenomic characterization of angina pectoris by determining miRNAs.

Coronary artery disease is traditionally understood as a phenomenon that begins with endothelial dysfunction and, as it progresses, progressively affects the entire coronary tree (55). Likewise, this process is considered to be delayed for a long period of time, which means that patients with coronary artery disease can present a very prolonged preclinical phase until the development of myocardial ischemia. However, once this phase of the disease has been reached, one of the main prognostic factors is the presence of ischemia. It is also worth highlighting the heterogeneity of the presentation of ischemic heart disease, with data showing that patients can have isolated microvascular or macrovascular involvement, as well as a combination of these (56).

To date, only a recent Spanish article (57) showing the usefulness of miRNAs to distinguish acute myocarditis from acute coronary syndrome has truly awakened the interest of clinical cardiologists in these promising disease markers in other types of pathologies. In relation to coronary artery disease, with the exception of the aforementioned work, the clinical relevance of miRNAs continues to be scarce. This may be due to the fact that the discovery of new markers that provide additional clinical information to that provided by clinical, biochemical or diagnostic imaging factors is difficult given the great development of research in these fields over the last several decades, especially in patients who survive acute myocardial infarction.

In our opinion, the great a priori strength of this investigation would lie in the robust determination of four comparison groups, with the most specific techniques for their characterization (coronary physiology studies), which would consider the three possible combinations of involvement of the compartments of the coronary tree (Groups 1 to 3) and a group of patients without ischemic heart disease (Group 4). Likewise, a final group (Group 5) would provide additional information on the presence of coronary spasm. The precise definition of these groups would allow a robust assessment of over or under-expression, and even the existence of gradients in miRNAs depending on the extent of myocardial ischemia and the number of coronary vascular compartments affected.

So far, few papers have evaluated miRNAs in a manner similar to our research proposal, such as in coronary endothelial dysfunction (7). However, to our knowledge, the role of miRNAs in relation to microvascular dysfunction such as IMR has not been specifically evaluated, nor has a study been developed that attempts to globally understand the role of miRNAs in relation to the coronary vascular compartments involved in the presence of myocardial ischemia.

It is also noteworthy that research on coronary physiology is experiencing a new boom, and in our opinion, contributions in this field would be very valuable. In addition, the determination of miRNA patterns could provide an opportunity to improve patient treatment and even reduce the need for invasive physiological tests. For all these reasons, we consider that the present study could be of great scientific interest.

In addition, a contingency plan will be established in the event that differences between miRNAs in the different study groups, since we will have a sample bank that will allow us to analyze other biomarkers where the research group has experience. Likewise, a dissemination plan aimed at the general public will be established, and actions will be carried out to inform segments of the population of special interest/vulnerability within the scope of the study. The information obtained will be made available to the scientific world and the general public in collaboration with the IRBLleida Communication Department. IRBLleida has taken several steps to disseminate scientific messages in a clear and understandable way. We will use the IRBLleida website (https://www.irblleida.org/es/) that contains information on projects, publications and research groups. To make research more accessible to society, we will use digital communication platforms. Additionally, some of the researchers are members of the European COST CardioRNA program (https://cardiorna.eu/). One of the working groups of this program is focused purely on the communication of the results obtained.

**ANALYSIS OF PROJECT FEASIBILITY.**

We consider the project to be viable for the following reasons. The Hemodynamics Unit of the University Hospital Arnau de Vilanova of Lleida performs more than 1,110 diagnostic coronary angiograms and more than 500 coronary angioplasties per year and, therefore, invasive coronary physiology studies could be carried out within a reasonable time period.

Similarly, the Institut de Recerca Biomèdica de Lleida has the necessary technology to carry out the processing, preservation of samples, and analysis of miRNAs, with extensive experience and publications in this field. In addition, at the Cardiology Service of the University Hospital Arnau de Vilanova of Lleida we have a Research Unit with a nurse specifically dedicated to this task, which ensures the protocolized extraction of sample.

It should also be noted that the Cardiology Department of the Arnau de Vilanova has experience in this field, as shown by the fact that it has conducted research on the validation and development of nonhyperemic coronary indexes (58), as well as pathologies presenting microvascular dysfunction, such as TakoTsubo syndrome (59).


**Anex 2: Recommendations to perform invasive physiological evaluation**(16,58,60)

| **First, RFR, FFR, CFR and IMR measurements will be performed as detailed below.** |
| --- |
| **Catheter Selection and Positioning**  • Use guide catheters (at least 5F) without lateral holes.  • Ensure coaxial cannulation of the guiding catheter in the coronary ostium.  • Decannulate the guiding catheter from the ostium to calibrate pressure, equalize, and record Pd / Pa if there is any doubt that the catheter may partially obstruct the ostium. |
| **Calibration**  • Before starting measurements, ensure that the aortic pressure is set to zero correctly (1/3 versus 2/3 chest diameter).  • Purge the pressure guide, place it in a horizontal position at the time of connection/calibration and do not move the pressure guide while performing the process.  • Before adjusting pressures, advance the guidewire until the pressure sensor is positioned exactly at the end of the guide catheter.  • Before equalizing the pressures, flush the guiding catheter with saline to remove the viscous contrast agent.  • Before equalizing pressures, remove the introducer and close the hemostatic valve.  • Pressure curves are usually averaged over three to five heartbeats. Therefore, the pressure equalization requires some time and artifacts should not occur during this time. |
| **Positioning of the Pressure-Temperature Guide**  • For the evaluation of epicardial lesions (RFR and FFR), the pressure sensor should be placed distal to the main vessel to be analyzed.  • RFR is measured first, followed by FFR, CFR, and IMR.  • For the determination of CFR and IMR, the pressure sensor should be placed in the distal segment of the vessel corresponding to the lesion to be evaluated.  • In the case of patients referred for coronary angiography who present a positive ischemia test, FFR, CFR and IMR will also be measured, in addition to the arteries of the lesions to be evaluated, in the arteries compatible with the ischemia detected in the ischemia test. Likewise, in the absence of lesions to be evaluated and a previous positive ischemia test to guide the exploration, the FFR, CFR and IMR will be evaluated in the anterior descending artery.  • A second guidewire, in addition to the pressure guidewire, could cause artifacts and should therefore be avoided.  • Detect artifacts: the sensor could interact with the wall of the vessel, especially in cases of narrow vessel caliber or severe tortuosity.  • Viscous contrast agent in the coronary artery may affect the pd/pa gradient. |
| **Hyperemia**  • Before advancing the pressure wire, administer nitroglycerin ic (usually 200 mcg) to prevent coronary spasm.  • Medications for hyperemia.  - Intravenous adenosine 140 μg / kg / min.  • In case of measurement results in the borderline area, an increase in the dose of ev adenosine is possible. However, intravenous doses> 180 μg / kg / min may reduce coronary perfusion and are therefore not recommended. |
| **Recording and Evaluation**  • Artifacts should be carefully observed and excluded.  RFR and FFR  • For the determination of RFR, a minimum of 5 consecutive cardiac cycles are required.  • After administration of intravenous adenosine, pressure values may decrease to a minimum before reaching steady state. Wait until stable FFR values are obtained.  • Values measured during atrioventricular block/adenosine-induced bradycardia should be classified as "not evaluable".  • Ectopic beats may falsify the values obtained, so be sure to obtain values during periods of electrically stable time.  CFR and IMR  • For the determination of CFR and IMR, 3 rapid injections of 3 cc of physiological saline will be made at baseline. Subsequently, during the administration of ev adenosine and once the state of maximum hyperemia is reached, 3 rapid injections of 3cc of physiological saline will be performed again.  • Alterations in the saline temperature or the saline injection rate may cause abnormal Tmn values that are detected by the software. Carefully evaluate the concordance of these values to assess whether any injection should be repeated.  • To determine the CFR, the Tmn information obtained at baseline and at maximum hyperemia is used. To determine the IMR, only the Tmn information obtained at maximum hyperemia is used. |
| **Then, QFR and IMRangio measurements will be performed according to the specifications detailed in the specific software.** |
| **Acetylcholine test will only be performed for patients in Groups 3 and 4 as detailed below.** |
| • Electrocardiographic monitoring of the patient by 12-lead electrocardiogram.  • Cinefluoroscopy images will be obtained in a cranial projection that adequately displays the anterior descending artery.  • Given the expected diffuse nature of coronary spasm, it will be performed by increasing injections of acetylcholine up to 3 doses of 2, 20 and 100 mcg in the left coronary artery.  • Acetylcholine injections will not be performed in the right coronary heart due to the very high risk of severe bradycardia.  • The intracoronary bolus administration time will be performed slowly for 20 seconds.  • The guiding catheter should then be slowly flushed with saline to prevent abrupt injections of the drug remaining in the catheter at the time of acquisition of the cinefluoroscopy image.  • After each injection, the presence of symptoms suggestive of angina and similar to those that motivated the study will be evaluated, a cinefluoroscopy image will be acquired and a 12-lead electrocardiogram will be performed.  • If significant angiographic spasm or ST elevation/decrease suggestive of microvascular or macrovascular spasm is documented, progression to the next dose will not continue.  • In case of significant spasm, as well as at the end of the test, 200 mcg of NTG ic will be administered to abolish the effect of acetylcholine. |

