**- Acetylcholine coronary vasoreactivity test** (1)**.**

Under normal conditions, an artery with a healthy endothelium responds to acetylcholine with release of nitric oxide, generating vasodilatation. In cases of blocking the action of the enzyme nitric oxide synthase or denuding the arterial wall of the endothelium, vasoconstriction is generated on the contrary, secondary to a stimulation of smooth muscle muscarinic receptors, not counteracted by nitric oxide of endothelial origin. Therefore, acetylcholine infusion can be used to assess endothelial function and adequate coronary vessel tonicity. A relevant percentage of patients with angina without associated obstructive coronary artery disease may present with this type of alteration. Although different methods have been used to reveal this entity, currently the most widely used currently is the intracoronary acetylcholine infusion test. Its objective to determine the presence of endothelial dysfunction or tonic alterations is based on the reproduction of symptoms, the triggering of vasoconstriction and the detection of electrocardiographic alterations. The evaluation of the results of this test is detailed below:

| **Intracoronary Acetylcholine Infusion Test: Diagnostic Criteria** | |
| --- | --- |
| - Negative with vasodilator response (normal):   -Non-clinical  -No ECG changes  -Vasodilation after Ach (with respect to baseline) | - Negative with vasoconstrictor response:   -Non-clinical  -No ECG changes  -No constriction ≥ 90% (with respect to NTG)  -Mild vasoconstriction (with respect to baseline) |
| - Epicardial vasospasm:   -Symptom recurrence  -ST rise or fall  -Constriction ≥ 90% (with respect to NTG) | - Microvascular vasospasm:   -Symptom recurrence  -ST-segment elevation  -No constriction ≥ 90% (with respect to NTG). |

Table 6. Intracoronary acetylcholine infusion test.

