**- Sample size estimation.**

Based on previous studies of our group and previous studies for the determination of miRNAs in the presence of coronary endothelial dysfunction, we have recruited around 40-50 patients to complete the investigation (7,48–50). In our case, we will study the relationship between miRNAs and the different patterns of involvement according to the affected coronary compartment, that is, Group 1 (Macrovascular and Microvascular Angina); Group 2 (Macrovascular Angina); Group 3 (Microvascular Angina); and Group 4 (Non-coronary chest pain). Given that Group 4 corresponds to patients without coronary circulation alterations, it will be used as a control group with respect to the other groups until recruitment of 25 patients per group is completed, in a similar amount to other control groups in similar studies, totaling 100 patients. Likewise, given the possibility that some patients may present macrovascular and/or microvascular spasms that could overlap with some of the other groups, Group 5 (Macrovascular or Microvascular Spastic Angina) has been defined and will not be included for the purposes of estimating the sample size.

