**- Diagnostic coronary angiography and physiological evaluation of the coronary tree.**

After diagnostic coronary angiography, a standardized analysis of coronary lesions in terms of percentage of stenosis and length of the lesion will be performed by quantitative coronary angiography (QCA), in order to avoid variability in visual estimation of coronary lesions. Subsequently, a functional assessment of epicardial lesions with a pressure guidewire will be performed, first with the measurement of nonhyperemic coronary indexes: "Resting full-cycle ratio" (RFR) and RFR adjusted for discordance predictors ("Adjusted RFR), and then by means of the hyperemic coronary indices "Fractional Flow reserve" (FFR), "Coronary Flow Reserve" (CFR) and "Index of Microcirculatory Resistance" (IMR) positioning the pressure guidewire in the distal segment of each artery to be evaluated, being able to interrogate more than one artery in the same patient. Similarly, in patients referred for coronary angiography who have a previous positive ischemia test and whose epicardial arteries are not considered tributary to evaluation, the pressure guide wire will also be placed in the artery corresponding to the territory compatible with the ischemia detected in the test. In the case of coronary lesions not susceptible to physiological evaluation, the pressure guide wire will be positioned in the distal segment of the anterior descending artery, evaluating the "Coronary Flow Reserve" (CFR) and the "Index of Microcirculatory Resistance" (IMR) in the territory of the anterior descending artery. Measurements will be obtained using the ″PressureWire™ X Guidewire 0.014" device (Abbott Vascular Inc., Santa Clara, CA,). For induction of hyperemia, adenosine will be used as a vasodilator drug. In addition, for each lesion the angiography-derived index "Quantitative Flow Ratio" (QFR) and for each artery the "Angiography-derived Index of Microcirculatory Resistance" (IMRangio) will be evaluated.

As for the performance of the coronary vaso-reactivity test, acetylcholine will be used as described above. Given the risk of epicardial spasm in case of macrovascular ischemia derived from epicardial lesions, the acetylcholine test will be performed only in patients who do not present pathological FFR values (> 0.80). More detailed recommendations for the performance of coronary physiology studies are presented in **Annex 2**.

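### Table 6 requires ST elevation for microvascular spasm, so a patient with provoked symptoms, ST depression and under 90% constriction fits no category and would by default stay among the Group 4 controls

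*Protocol*

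**What the plan says.** The protocol section on the acetylcholine vasoreactivity test presents Table 6 as the way its results are evaluated. The table has four categories: two negative and two spastic. Both negative categories require no symptoms and no ECG change. Both spastic categories require symptoms to recur. They differ in constriction (at least 90% relative to nitroglycerin for epicardial spasm, less for microvascular spasm) and in the ECG criterion: "ST rise or fall" for epicardial spasm, but "ST-segment elevation" alone for microvascular spasm.

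Annex 2, on the conduct of the test, says: "If significant angiographic spasm or ST elevation/decrease suggestive of microvascular or macrovascular spasm is documented, progression to the next dose will not continue".

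The section on determining the coronary pattern says that "the angina pattern corresponding to each patient will be determined, based on the values of FFR, CFR and IMR". For the patients tested with acetylcholine (Groups 3 and 4) it adds: "Patients presenting macro or microvascular spasm in this test will be included in Group 5". It gives no rule for a result that is neither spastic nor negative.

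The sample size section fixes the role of Group 4: "Given that Group 4 corresponds to patients without coronary circulation alterations, it will be used as a control group". The section on scientific interest describes the same group as free of ischaemic heart disease and rests the study's strength on precisely defined groups.

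**The concern.** Group membership is the comparison variable of the primary objective, and Group 4 is the reference for the other groups. Its value as a reference depends on its members having no coronary abnormality. A patient whose angina is reproduced by acetylcholine, with ST depression, does not fit that description. If Table 6 is applied as written, the direction of the ST shift alone decides whether this patient counts as having spasm.

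A second problem is consistency between operators. One who follows Table 6 finds no spasm and leaves the patient where FFR, CFR and IMR placed them. One who has stopped the test because ST depression suggested spasm may assign Group 5. The protocol does not say which is right.

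**Working it through.** The protocol states no figure that depends on this rule, so the check sets the texts side by side.

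**Patient considered:** FFR > 0.80, IMR < 25 and CFR ≥ 2.0, so Group 4 before the acetylcholine test. On acetylcholine: symptoms recur, ST depression, constriction below 90% relative to nitroglycerin.

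| Table 6 category | Symptoms required | ECG required | Vessel response required | Met? |
|---|---|---|---|---|
| Negative, vasodilator | None | No change | Dilation from baseline | No: symptoms and ECG change |
| Negative, vasoconstrictor | None | No change | Mild constriction from baseline, below 90% | No: symptoms and ECG change |
| Epicardial spasm | Recurrence | ST up or down | At least 90% | No: constriction too small |
| Microvascular spasm | Recurrence | ST up only | Below 90% | No: ST direction only |

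**Step 1.** No category is met. The microvascular row fails on one item, the direction of the ST shift. The same patient with ST elevation would have microvascular spasm.

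**Step 2.** Under Annex 2, ST depression judged suggestive of either type of spasm ends dose escalation. The test may therefore stop for suspected spasm in a patient whom Table 6 does not call spastic.

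**Step 3.** The pattern section takes the group from FFR, CFR and IMR and moves only patients with spasm to Group 5. Without a spasm label nothing moves this patient, so Group 4 stands by default.

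**Step 4, after the fix.** If the microvascular row accepts ST elevation or depression, the patient meets it and goes to Group 5.

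**Scale.** The plan is 25 patients per group, so one such patient is 1/25 = 4% of the controls, two are 2/25 = 8% and three are 3/25 = 12%. Suppose, as an assumption, that these patients carry the mean miRNA level of the group being compared with controls. With a share *m* of them among controls, the expected difference in means becomes (1 − *m*) times the true one: 0.96, 0.92 and 0.88. These counts are illustrative. The protocol gives no frequency, and the number could be zero.

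**The case against.** The strongest reply is that Annex 2 contains a dose-stopping rule, not a diagnostic definition, and that a safety stop may properly be wider than a diagnosis. Its wording also covers the two spasm types jointly. It is compatible with Table 6 if elevation may indicate either type and depression only the epicardial type. This stands. A reader might infer that the protocol defines microvascular spasm in two contradictory ways; the text does not support that. What remains needs no contradiction, because Table 6 on its own leaves the patient without a category.

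A reader might also infer that the protocol assigns such patients to the controls. It does not say so. The patient is unclassified, and staying in Group 4 follows only from the absence of a rule that moves them. An investigator could defend Group 5. That freedom is part of the problem.

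It is tempting to extend the point to Group 3. That is weak: a Group 3 patient has IMR of at least 25 or CFR below 2.0, so the microvascular label remains true, and the sample size section already recognises that spasm may overlap with other groups.

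The link from conduct to Table 6 can be questioned too. The sentence "As for the performance of the coronary vaso-reactivity test, acetylcholine will be used as described above" concerns performing the test, and its section then refers to Annex 2 for detail. The firmer link is the acetylcholine section itself, which introduces Table 6 as the evaluation of results.

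Finally, the elevation-only criterion may be deliberate. The documents cannot settle that, so the change needs clinical confirmation. Nor is this merely detail for an analysis plan: the protocol itself fixes the diagnostic criterion, and the criterion decides who is a control.

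**Conclusion.** The point holds in a limited form. Table 6 leaves one clinically meaningful result (recurrent symptoms, ST depression, constriction below 90%) outside every category. With normal FFR, CFR and IMR, the patient would by default stay in a control group described as having no coronary circulation abnormality. The microvascular row stands apart from both the epicardial row and the Annex 2 wording, which suggests a slip but does not prove one.

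The conclusion assumes that Table 6 is applied literally and that a patient not labelled as having spasm keeps the group given by FFR, CFR and IMR. The size of the effect on the miRNA comparisons is unknown. The stopping rule is sound and is not in question. The change is worth making because it protects the reference group at little cost.

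**What to change.** 1. In Table 6, change the ECG criterion for microvascular spasm to ST elevation or depression, once the clinical team confirms it. Patients with recurrent symptoms, ST depression and less than 90% constriction then go to Group 5.
2. In the section on determining the coronary pattern, add a sentence: of the patients with normal FFR, CFR and IMR, only those with a negative Table 6 result stay in Group 4; any other result that is not spasm is kept out of the control comparison, whether or not dosing was stopped early.
3. Leave the Annex 2 stopping rule unchanged.

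Cost: one criterion and one sentence. No new measurement is needed, because Annex 2 already has symptoms, a 12-lead ECG and a cine image recorded after each injection. The downside is recruitment. Group 5 lies outside the sample size, so each control who is moved or set aside must be replaced to reach 25. If the clinical team keeps elevation only as a deliberate criterion, the second change alone still protects the controls.
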